### **Tool for testing smell function: TWSIT**

Shen et al conducted a market survey and identified eight odorants, including 1. honey peach, 2. passion fruit, 3. cantaloupe, 4. lemon, 5. smoked plum, 6. garlic, 7. coffee, and 8. jasmine with a high identification rate (more than 95%) for 1000 Taiwanese. Then, based on the 8 odors, they developed a tool for smell identification specific for Taiwanese, the TWSIT

questionnaire consisted of multiple-choice questions. Correlational analysis was done for TWSIT and TC-UPSIT and the Spearman’s rho correlation coefficient between the two methods was 0.874 ( $p < 0.01$ ), which indicated the newly developed tool had well validation with TC-UPSIT

### **Testing method of TWSIT**

The device uses a sticker containing special odor molecules to determine whether the patient's sense of smell is lost and its severity by identifying the type of odor. The process of using this tool is described as follows:

1. The device contains a total of 16 questions, the first 8 questions are the same as the last 8 questions, but the order is different. Each question contains 2 sub-questions (Zone A and B). A total of 32 columns should be filled in and one is indispensable.
2. The patient uses a pencil to draw the olfactory block in the test book. This action will release the odor molecules contained in this block.
3. The patient approaches this block for about 1 cm with his or her nose and smells the smell of this block to answer the questions about the smell.
4. Each question contains two parts that need to be answered: Zone A and B. In Zone A, the patient needs to answer what he or she smells (there are four options for the question and cannot be blank). In Zone B, the patient must answer that the answer just now is 1. guess, 2. smell but not sure, 3. did smell, and he or she must choose one of the three, not blank.
5. After answering questions 1 to 8, the patient should take a rest for at least 1 minute. During the break, he or she should open the back page of page 8 and use various angles of the pencil to fill the box to remove the odor molecules attached to the pencil, which can avoid affecting the answering of subsequent questions. After waiting for 1 minute, the patient should continue to answer the 9 to 16 questions.
6. After completing the 16 answers, the patient hands over the testing device to a research-assistant for scoring.

**Note 1:** If the patient smells any smell, but cannot find the corresponding answer in the options, choose a similar smell to answer. In this case, "*smell but not sure*" should be marked in Area B, and "guess" should not be marked.

**Note 2:** There is only one situation in which the patient can choose the "guess", and that is when he or she can't smell anything at all.

### Scoring method

The scoring method of the olfactory testing device is explained as follows:

1. Zone A: 1 point for correct, 0 point for wrong.
2. Zone B: 0 point for "guess", 1 point for "smell but not sure", 2 points for "did smell".

**Note 1:** Zone A fills in error and zone B fills in "smell but not sure" to get 1 point.

**Note 2:** Zone A fills in error and zone B fills in "did smell" to get 0 point.

The testing book has a total of 16 questions; the maximum score for the zone A is 16 points, and the maximum for the zone B is 32 points. Summing the scores of zone A and B gets a full score of 48 points. According to the score, it can be judged that the sense of smell is *normal*, *hyposmia*, or *anosmia*.

| Age / Olfactory status | Anosmia     | Hyposmia     | Normal       |
|------------------------|-------------|--------------|--------------|
| 20-35 years old        | 0-11 points | 12-43 points | 44-48 points |
| 36-55 years old        | 0-11 points | 12-42 points | 44-48 points |
| 56-80 years old        | 0-11 points | 12-39 points | 40-48 points |

**Note:** The results of examinations under 19 years of age are interpreted according to the standard of 20-35 years; results of persons over 81 years of age are interpreted according to the standard of 56-80 years old.

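### The TWSIT cut-off row for ages 36-55 leaves a score of 43 in no category, so hyposmia and normal smell are not fully defined for that band

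*Protocol*

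**What the plan says.** The Scoring method section of the protocol builds the TWSIT total from 16 questions. On the zone maxima it states that "the maximum score for the zone A is 16 points, and the maximum for the zone B is 32 points", and then "Summing the scores of zone A and B gets a full score of 48 points". It goes on: "According to the score, it can be judged that the sense of smell is" normal, hyposmia or anosmia, and gives a table of limits by age.

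- Ages 20-35: anosmia 0-11, hyposmia 12-43, normal 44-48.
- Ages 36-55: anosmia 0-11, then "12-42 points | 44-48 points" for hyposmia and normal.
- Ages 56-80: anosmia 0-11, then "12-39 points | 40-48 points" for hyposmia and normal.

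Three other places bear on the point. The Patients section excludes anyone whose screening TWSIT shows anosmia. The Statistical analysis section applies a t test to the variation in TWSIT scores. The opening Background and Purpose section and the section on gaps in past research ask when olfactory disorder appears after radiotherapy, whether it recovers, and how long recovery takes.

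**The concern.** A cut-off table should place every possible total in exactly one category. In the 36-55 row, hyposmia stops at 42 and normal starts at 44. The rows above and below leave no such gap, so this looks like a wrong limit and not a deliberate indeterminate zone.

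This table is the only place where the protocol separates hyposmia from normal smell. A patient aged 36-55 who scores 43 at a visit can be called neither affected nor recovered. Whoever classifies the data would have to leave that visit out or choose a side, possibly after seeing results. That bears on onset and recovery, which are the questions the study sets out to answer.

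**Working it through.** **Inputs, all from the Scoring method section.** There are 16 items. Zone A gives 1 point for a correct answer and 0 for a wrong one. Zone B gives 0, 1 or 2 points by certainty. Two notes cover wrong zone A answers: a wrong answer with an unsure rating scores 1, and a wrong answer with a definite smell rating scores 0.

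**Step 1: reproduce the full score.** 16 × 1 + 16 × 2 = 16 + 32 = 48, which agrees with the protocol.

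**Step 2: can 43 occur?** Under these rules an item scores 0, 1, 2 or 3. Adding 16 such items reaches every total from 0 to 48. For 43: 11 × 3 + 5 × 2 = 33 + 10 = 43.

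**Step 3: classify every total from 0 to 48 as the table is printed.**

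| Age band | Hyposmia ends | Normal begins | Totals with no category |
|---|---|---|---|
| 20-35 | 43 | 44 | none |
| 36-55 | 42 | 44 | 43 |
| 56-80 | 39 | 40 | none |

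No total falls in two categories. The gap is the single score 43, in the single band 36-55.

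**Step 4: test both ways of closing it.** With normal as 43-48, or with hyposmia as 12-43, every total in the band falls in exactly one category. Either change repairs the table, so the arithmetic cannot show which limit is the misprint.

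**Step 5: how often might 43 occur?** The protocol gives no response rates, so this is illustration only. Assume 16 independent items, a probability p of a correct answer, a probability q of a definite smell rating, and an unsure rating otherwise. Per item, the chance of 3 points is pq, of 2 points p(1−q), of 1 point (1−p)(1−q), and of 0 points (1−p)q. Summing 16 items exactly gives:

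| p | q | P(total = 43) |
|---|---|---|
| 97% | 90% | 0.088 |
| 95% | 90% | 0.106 |
| 95% | 80% | 0.143 |
| 97% | 70% | 0.164 |
| 90% | 70% | 0.079 |
| 85% | 70% | 0.042 |
| 80% | 70% | 0.020 |
| 70% | 60% | 0.002 |

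The share runs from roughly 8-16% when smell is near normal to almost nothing when loss is marked. Independence is itself doubtful, because questions 9-16 repeat questions 1-8 in another order.

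**The case against.** The strongest case against giving this much weight is that nothing the protocol commits to depends on the gap. A 43 enters the t test like any other number. Eligibility turns only on anosmia, which is 0-11 at every age. No endpoint or recovery rule based on the categories is written down. All of this stands and limits the severity. It does not remove the point, because the study asks about disorder and recovery and this table is the only stated line between hyposmia and normal. A one-digit error in the conversion from PDF cannot be fully excluded, but the cells read as complete and nothing suggests one.

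A reader might infer three stronger things that the documents do not support.

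- *That the age bands create false recoveries.* The normal limit falls to 40 at age 56, so an unchanged score of 40, 41 or 42 would move from hyposmia to normal if the band followed current age. The protocol does not say that it does. Age-specific norms are ordinary, and the choice between baseline and current age may sit in an analysis plan that is not shown. The effect would also be small. With ages assumed even over 40-75 and about 14 months of observation, 1.17/35 = 3.3% of patients cross the edge. In the first four scenarios of the table above, P(40-42) is 0.11 to 0.39, which gives about 0.4 to 1.3 patients per 100.
- *That a definite number of assessments will be unclassifiable.* With 100 patients, 6 visits and an assumed 40% aged 36-55, there are 240 assessments in the band. At 0.079 to 0.164 that is about 19 to 39, but only if smell stays near normal at every visit, in a study of smell loss. At 0.020 to 0.042 it is about 5 to 10.
- *That normal must be 43-48 because the limit should fall with age.* Only two sound values are available, 44 and 40. They fit 44/43/40 and 44/44/40 equally well.

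**Conclusion.** The point holds as a narrow error on the page. For ages 36-55 the attainable score 43 has no category, and one limit in that row is wrong. This needs no assumption beyond the printed table and scoring rules.

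The consequence is confined to the split between hyposmia and normal, and so to counts of patients who develop or recover from hyposmia. The numeric-score test and the anosmia exclusion are unaffected. The number of assessments involved cannot be derived from the documents; the percentages given rest on assumed response rates and independent items. Severity is minor to moderate.

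**What to change.** Reconcile the 36-55 row with the instrument's own norm table, so that every total from 0 to 48 falls in exactly one category. Whether the row should read hyposmia 12-43 or normal 43-48 has to come from that source. Make the correction before any data are classified; the project timetable plans a preliminary analysis in the first year. The cost is one table cell.

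As an optional safeguard, not the correction of an error, add one sentence saying that a patient's age band at baseline is used at all visits. An unchanged score of 40-42 then cannot change category when a patient turns 56. Closing the gap does not achieve this by itself, since those scores would still switch under either repair if current age were used.

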## **SNOT-22**

SNOT-22 is a subjective assessment tool commonly used to assess the severity of sinusitis. At each time point of smell assessment, we will apply the tool to evaluate the subjective symptoms of sinusitis in those NPC patients.

There are 22 questions in the tool and each question is divided into 1. no problem, 2. very mild problem, 3. moderate problem, 4. severe problem, and 5. problem as bad as it can be. According to the severity, each problem corresponds to 0 to 5 points. After the patient has checked the severity of each question, all the scores are summed up.

## **Endoscopic evaluation**

Because patients with H & N cancer received IMRT, there is a high incidence of causing sinusitis. Further, sinusitis generally also affects olfactory function, which will lead to errors in olfactory evaluation. Therefore, at each time point of the olfactory evaluation, we perform nasoendoscopy (OLYMPUS EVIS EXERA II CLV-180; OLYMPUS EVIS EXERA II CV-180; OLYMPUS ENF-VQ / VT2) to investigate whether sinusitis occurs; besides, we also observe the state of olfactory cleft to see whether the space is obliterated by the edematous nasal mucosa.

The key parts of endoscopic evaluation and recording include: 1. inferior turbinate, 2. middle meatus, 3. olfactory cleft, and 4. nasopharynx. In addition, if sinusitis is found, appropriate treatment will be given. During the follow-up period, the endoscopy will be repeated to evaluate whether the sinusitis is completely resolved, and a second smell-associated assessment will be made.

### **Modified Lund Kennedy endoscopic system**

The modified Lund Kennedy (MLK) system is a common scoring tool to evaluate and quantify the severity of sinusitis. Therefore, we will use the scoring tool for each endoscopic evaluation. The MLK system is divided into three assessment aspects: 1. nasal polyps: “no” for 0 point, “limited in the middle meatus” for 1 point, and “exceeding the middle meatus” for 2 points; 2. edema: “no” for 0 point, “slight” for 1 point, “severe” for 2 points; 3. secretion: “no” for 0 point, clear secretion for 1 point and thick or purulent discharge for 2 points. After the nasal cavity on both sides are examined separately, the scores are summed. The maximum score on one side is 6 points; the maximum score on both sides is 12 points.

### **Acoustic rhinometry**

The olfactory epithelium is above the space of olfactory cleft. In addition to using nasoendoscopy to directly observe the changes in the state of this area during IMRT, we also apply acoustic rhinometry to subjectively evaluate the nasal resistance and volume for this region.

The examination can generate three sets of data (A. nasal resistance, NR and B. minimal cross- area, MCA) for 1.the nasal valve, 2.the middle part of nasal cavity, including the middle meatus and olfactory cleft, and 3. nasopharynx.

### **Measurement process**

The patient adopts a standing posture, and the research assistant first makes a validation for the device (5 seconds), and then measures the nasal cavities on both sides. During the detection process, the patient needs to hold his or her breath for about 5-10 seconds in accordance with the instructions of the assistant. The assistant records the data of nasal resistance and cross-sectional area of the patient's bilateral nasal cavity for subsequent analysis.

**Specific aim 2:** Investigating the association between the IMRT-related olfactory dysfunction and nasal microenvironment

We collect the patient's nasal secretions and analyze the levels of cytokines at the time points when the patient was accessed with olfactory-related tests. Further, investigations will be conducted to analyze if it exists any correlation between the changes in the nasal microenvironment and IMRT-related olfactory dysfunction.

[figure not shown]

### Sample collection

A pledget (8x2x0.2cm) will be placed gently into the anterior nasal cavity of patients for 10 minutes. After removal of the pledget containing nasal secretion, it will be put into the inner tube of a mini spin column (Epoch Life Science Inc.), which filter is removed in the preceding procedure. Centrifugation with 10000 bpm for 10 minutes will be performed and we will collect the nasal secretion separated from the pledget for further analysis and the samples will be stored at -80°C.

### Sample analysis - Flow cytometry with cytometric bead array (CBA)

Soluble Th1-related cytokines including IL-1 beta, TNF-alpha, IFN-gamma and Th2-related cytokines, including IL-4, IL-6 and IL-10 will be measured by multiplexed cytometric bead array (CBA; BD Biosciences, San Jose, CA, USA). The CBA will be conducted according to the

manufacturer's instructions. A master cocktail containing the proteins of interest (as supplied by BD Biosciences) at a concentration of 5000pg/mL in CBA assay diluent will be prepared. 10 standard solutions of the following concentrations will be then prepared using the standard diluent (BD Biosciences): 5000 pgmL, 2500 pgmL, 1250 pgmL, 625 pgmL, 312.5 pgmL, 158.25 pgmL, 78.125 pgmL, 39.0625 pgmL, 19.53125 pgmL and 0 pgmL. The capture beads supplied with the kit for the proteins of interest will be vortexed for 15 seconds and diluted 1:100 in bead diluent to make up the bead cocktail. 25µL of the bead cocktail will be added to 25µL of samples/standards in a 96-well plate. The plate will be mixed on a shaker at 500rpm for 5 minutes before incubating for 1 hour at room temperature. The detector cocktail will be prepared in the same way as the bead cocktail, substituting the capture beads for detector antibodies (as per the BD manufacturer's protocol) and the bead diluent for detector diluent. 25µL of the detector cocktail will be then added to the wells and the plate mixed as before and left to incubate at room temperature for 2 hours. After incubation will be completed, 200µL of wash buffer (BD Biosciences) will be added to each well and the plate centrifuged at 1300rpm for 10 minutes at room temperature. The supernatant will be discarded, and the beads re-suspended in 50µL of wash buffer before being transferred into a tube for analysis. A BD FACS Canto II Flow Cytometer will be used to measure the fluorescence of the samples/standards. Using the FACS Array software version 3.0.1 (BD Biosciences), the mean fluorescent intensities of the standards will be used to generate a standard curve for each protein of interest. The mean fluorescent intensities of the samples will be measured against the standard curve to give the concentrations of the proteins in pgmL.

### **Statistical analysis**

The sample size was based on a power of 80%. Using a two-tailed *t* test with  $p < 0.05$ , we

estimated the sample size as 60 participants, with an allowance for a potential dropout rate of 20%. The demographic characteristic and comorbidities of those H & N cancer cases are described as mean with standard deviation. Student *t* test will be used to analyze the variation of TW-SIT scores and the results would be plotted as multiple sloping chart. All data were analyzed using Microsoft Excel and MedCalc statistical software. A *p* value of <0.05 was considered statistically significant.

## Anticipated Results:

Timetable of this project is listed following:

### **The first year**

1. Recruit 40 newly diagnosed H & N cancer patients and complete evaluation, including TW-SIT, SNOT-22, endoscopy, acoustic rhinometry and collection of nasal secretion.
2. Make the preliminary analysis, including the alternative trend of olfactory function before and after IMRT and the correlation between the changes of smell and nasal microenvironment.
3. Write the interim report.

### **The second year**

1. Recruit another 40 newly diagnosed H & N cancer patients, complete evaluation and make the analysis.
2. Write the interim report.

### **The third year**

1. Recruit another 20 newly diagnosed NPC patients, complete evaluation and complete the analysis.
2. Write the final report.
3. Submit the manuscripts to SCI journals.

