### **Methods:**

The research population of this study is newly diagnosed H & N cancer patients who receive curative IMRT at Chiayi Chang Gung Memorial Hospital during the study period. It is estimated that 100 patients will be enrolled in three years. Before RT, at the end of RT, one month, three months, six months and one year after RT, those patients will be tested by the Taiwan version of the olfactory assessment tool to evaluate their olfactory status. In addition, the Taiwan version of Sino-nasal Outcome Test-22 will be used to assess the subjective nasal symptoms of those H & N cancer patients. Nasal endoscopy will be performed to investigate and record the state of the nasal cavity of them, and we will collect those patients' nasal secretions for testing to analyze the changes in the nasal microenvironment.

Keywords : Loss of smell, Olfactory dysfunction, Hyposomnia, Anosmia, head and neck cancer, radiotherapy, IMRT

Please provide an overview of the anticipated impacts that the implementation of this project may have on various aspects, including social, economic, and academic development, in no more than 150 words.

Loss of smell can reduce the quality of life, sometimes cause danger, such as inability to smell harmful substances, and reduce the taste of food and cause nutritional disorders. Based on the findings of this study, we can comprehensively realize the effect and prognosis of RT on the olfactory function in H & N cancer patients. Then, on the basis of this research, we will have the opportunity to research and develop effective therapies for preventing, attenuating or treating the radiation-associated complication.

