### Patients

This study will enroll 100 patients initially diagnosed with H & N cancer at the Chiayi branch of Chang Gung Memorial Hospital in three years. The inclusion criteria include 1. patients should be older than 20 years old, 2. the H & N cancer treatments should contain IMRT, and 3. they should be willing to sign an informed consent approved by the institutional review board. The exclusion criteria include 1. patients with severe olfactory dysfunction (anosmia) and 2. patients with sinusitis before H & N cancer treatment.

**# Note 1:** we will apply TWSIT to screen patient's olfactory state and if the result is anosmia, the patient will be excluded.

**# Note 2:** If a patient is found to have sinusitis before treatment for H & N cancer, but if the sinusitis is completely resolved after adequate treatment before IMRT, the patient can still be included in this study.

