### **Time points of evaluation**

The time points for olfactory-associated assessments in the study include 1. before IMRT, 2. at the time of IMRT completed, 3. 1, 3, 6, and 12 months after IMRT. At each time points, the results of examination will be labelled as “primary assessment”. However, if sinusitis is noted at the primary assessment, adequate treatment will be given, and an intact evaluation will be repeated if the sinusitis is completely resolved. The results of repeated evaluation will be labelled as “secondary assessment”.

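### The third-year timetable cannot be met together with the 12-month visit: at least 20 of 100 patients would have no 12-month data when the final report is written

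*Protocol*

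**What the plan says.** Protocol, *Methods*, gives the enrolment period: "It is estimated that 100 patients will be enrolled in three years". The *Patients* section repeats the target of 100. The timetable under *Anticipated Results* divides it into 40 patients in the first year, 40 in the second and 20 in the third.

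For the third year the instruction is "Recruit another 20 newly diagnosed NPC patients, complete evaluation and complete the analysis", followed by "Write the final report" and submission of manuscripts.

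*Time points of evaluation* sets the visits: one before IMRT, then "at the time of IMRT completed, 3. 1, 3, 6, and 12 months after IMRT". The follow-up clock therefore starts at the end of IMRT, not at enrolment.

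No follow-up period after the third year is described. The protocol has no rule for patients whose 12-month visit falls after the final analysis.

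**The concern.** Two parts of the same protocol cannot both be carried out. The visit schedule promises every patient an assessment one year after IMRT. The timetable closes evaluation, analysis and report in the year in which the last fifth of the patients is still being recruited.

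Whether smell recovers after radiotherapy, and how long that takes, are among the questions the study is set up to answer (*Background and Purpose*; *Lack of the past researches*). Prognosis is part of Specific aim 1. The 12-month visit is the latest information on those questions. If the timetable is followed as written, that visit is missing for a fifth or more of the cohort for calendar reasons alone, and nothing in the protocol tells the reader of the final report to expect it.

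**Working it through.** **Inputs from the protocol.** Enrolment is 40, 40 and 20 in years one, two and three (*The first year*, *The second year*, *The third year*). The last visit is 12 months after the end of IMRT (*Time points of evaluation*). Final analysis and report fall in year three. *Statistical analysis* gives 60 participants with a 20% dropout allowance, 80% power, and a two-sided t test at 0.05.

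**Assumptions not in the protocol.** Year three ends at month 36. Accrual is even within each year. IMRT starts at enrolment, which favours the plan. The IMRT course lasts 0 to 2 months. Dropout by 12 months is 20%. No time is reserved for closing the database unless stated.

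**Step 1: the protocol's own figure.** The 60 participants cannot be reproduced, because no effect size or standard deviation is given. Two readings are possible:
- If 60 includes dropout, the completers needed are 60 × 0.8 = 48.
- If 60 is the number of completers, enrolment should be 60 / 0.8 = 75.

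For a paired t test at 80% power these imply standardised changes of about 0.41 (n = 48) and 0.37 (n = 60).

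**Step 2: last useful enrolment month.** A patient enrolled at month t has the 12-month visit at t + IMRT duration + 12. For this to fall by month 36, t must be at most 24 − IMRT duration.

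**Step 3: patients enrolled by then.** For a cut-off c between months 12 and 24, the number is 40 + 40 × (c − 12)/12.

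| IMRT course (months, assumed) | Cut-off c | Can reach 12 months | Cannot | After 20% dropout |
|---|---|---|---|---|
| 0 | 24 | 80 | 20 | 64 |
| 1 | 23 | 76.7 | 23.3 | 61.3 |
| 1.5 | 22.5 | 40 + 40 × 10.5/12 = 75 | 25 | 60 |
| 2 | 22 | 73.3 | 26.7 | 58.7 |

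The first row's 20 is a floor. It does not depend on accrual shape, dropout or IMRT duration, because all 20 third-year patients enrol after month 24. If 3 months were also kept for close-out with a 1.5-month course, the cut-off is 19.5 and 40 + 40 × 7.5/12 = 65 could contribute, or 52 after dropout.

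**Step 4: the 6-month visit.** The cut-off is 30 − IMRT duration. With zero duration, 80 + 20 × 6/12 = 90 can be observed. With 1.5 months, 80 + 20 × 4.5/12 = 87.5. The earlier visits are much less affected.

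**Step 5: set against the 60 participants.** Power of the paired t test, using the standardised changes from Step 1:

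| Patients with 12-month data | If 48 completers were intended | If 60 completers were intended |
|---|---|---|
| 64 | 90% | 83% |
| 60 | 88% | 80% |
| 52 | 83% | 74% |

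**Step 6: when the last visit would occur.** If accrual uses all three years, the last patient's 12-month visit is at 36 + 1.5 + 12 = month 49.5.

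**The case against.** The strongest reply is that this is a brief yearly outline under *Anticipated Results*. It sets no data-cut date and no instruction to discard later visits, and the handling of visits not yet reached is commonly left to an analysis plan. The last part is fair. But the conflict is not about a missing detail: the protocol itself places completed evaluation, completed analysis and the final report in a year that its visit schedule rules out. Reading completed evaluation as baseline testing does not help, since the analysis and report stay where they are.

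A second reply is that recovery is also informed by the visits at 1, 3 and 6 months, and that no recovery endpoint is formally defined. Both points stand and they limit the damage. They do not restore the 12-month data.

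Four stronger readings are tempting, and the protocol does not support them:

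- **That calendar loss uses up the dropout allowance.** The allowance, "with an allowance for a potential dropout rate of 20" per cent, belongs to a calculated 60 participants, not to the planned 100. The plan enrols 40 more than the calculation asks for.
- **That the study is underpowered at 12 months.** With 60 to 64 patients, either reading of the 60 is met. A 2-month course (58.7) or a 3-month close-out (52) falls short only on the stricter reading. The calculation names no effect size, standard deviation or time point, and no target of 80 completers from which precision could be said to fall.
- **That years one and two have the same defect.** The first year asks for a preliminary analysis, and both years end in an interim report. There, completing evaluation can mean carrying out the listed test battery. Interim reports on the visits reached so far are ordinary practice.
- **That the missing patients are selectively NPC.** Only the third-year entry says NPC; the *Patients* section says "This study will enroll 100 patients initially diagnosed with H & N cancer". That may be a slip of wording. It should be reconciled, but it does not establish selective loss.

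**Conclusion.** The timetable and the visit schedule are incompatible and one of them must change. At least 20 of 100 patients cannot have the 12-month assessment by month 36; this follows from the protocol's own dates, once month 36 is taken as the end of the third year. Under even accrual within years and a 1.5-month IMRT course, about 25 cannot, 75 can, and about 60 would have 12-month data after 20% dropout. The consequence is thinner 12-month evidence on recovery and its timing, unannounced in the plan. A shortfall in power is not shown.

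**What to change.** **Preferred.** Place the final data cut and the final report after the last patient's 12-month visit. If accrual uses all three years and IMRT takes about 1.5 months, that is about month 49 to 50. Amend *The third year* accordingly.

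**If month 36 is fixed.** State in the protocol that only patients enrolled by about month 22 can contribute at 12 months. Give the expected number, about 75 before and about 60 after 20% dropout, with the assumptions behind it. Analyse all patients' available visits in a mixed model, treating visits beyond the data cut as administratively censored, so that later recruits still inform the earlier time points. That approach relies on late recruits not differing systematically from early ones, which is a further reason to reconcile the NPC wording.

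**Cost.** Either a later report or a less favourable 12-month figure. No extra patients or procedures are needed.
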